#### Concealment mechanism and Implementation

After the baseline session, an attribution request is then emailed, including the ID, to a researcher responsible for the attribution process with the QMinim software. This researcher does not participate in the follow-up assessment. This researcher then sets up the appointment with the clinician of the assigned arm.

### Assignment of interventions: Blinding

#### Who will be blinded

The statistician will be blind to the content of the intervention arm that will be called “A” and “B”. The neuropsychologists who perform the baseline assessment do not know about the randomisation (which is only carried out after the visits). The neuropsychologists that will be in charge of follow-up will also be blinded to the arm of the intervention. Patients will be warned to not mention their intervention arm or provide information that could cue the clinician (this will be reminded before each assessment session). If the clinician becomes unblinded during the testing session, this will be reported in the eCRF.

The person administering the intervention cannot be blinded, as the content is different. The participants cannot be blinded. However, the trial will be presented as “assessing the positive effect of two interventions on post-covid cognitive difficulties” Our prediction (superiority of the cognitive intervention) will not be communicated to the participants until the end of the trial (last follow-up for the last participant included).

#### Procedure for unblinding if needed

Not applicable: the patients and the clinicians know the intervention as the content of the sessions is different in the two arms.

### Data collection and management

#### Plans for assessment and collection of outcomes

All tests and questionnaires are administered by a trained psychologist specialized in neuropsychology. The primary outcome is administered via a computerized questionnaire system in the eCRF (Castor). MMQ and BRIEF (primary outcome) will be remotely administered again after a 2-week interval to take account of fluctuating difficulties.

#### Plans to promote participant retention and complete follow-up

Patients will be reminded by the researcher to log in and complete assessments.

#### Data management

The data are entered into the eCRF by the clinician researchers in charge of the evaluation. A manual was written to guide the encoding. Double entries were made on the first patients. 100% of the primary and 10% of the secondary outcomes are verified by independent monitor of Antwerpen University Hospital Clinical Trial Centre (UZA CTC). Last checks for data values will be done by the statistician and the data manager of UZA CTC.

#### Confidentiality

Confidentiality and data protection will comply with European and Belgian directives on the protection of individuals with regard to the processing of personal data and on the free movement of such data (GDPR). Standard operating procedure (SOP) for data protection are detailed on the website of the Faculty of Psychology EC (https://www.fplse.uliege.be/cms/c_4511361/fr/psy-comite-d-ethique). We will benefit from the procedures developed by the Data Protection Officers (DPO) at Liège university and CHU.

Personal information and linking code will be saved in a location separate from the one where data were collected, in encrypted, password-protected folders. Access to these data will be limited to only those who need it for the purposes of trial management, quality control, audit, and analysis. These data will be destroyed 5 years after the end of the trial.

Data entered into the eCRF will be coded and pseudo-anonymized. Computers used for storage of personal and research data are professional (not personal) laptops, protected by password. The folders where information will be stored will be also protected by password, and temporarily backuped on an encrypted external device stored in the researcher office.

#### Plans for collection, laboratory evaluation and storage of biological specimens for genetic or molecular analysis in this trial/future use

Not applicable for this study.

## Statistical methods

### Statistical methods for primary and secondary outcomes

#### Summary of baseline data and flow of patients

Preliminary analyses will be conducted to ensure comparability of both groups on demographic (sex, age, education years) and clinical characteristics at baseline. Two-sided independent sample t tests will be conducted for continuous variables and categorical variables will be analyzed with Fisher exact tests. A consort flow diagram will be produced to get an overview of the number of patients available at each stage: eligibility, allocation, discontinuation, short and long-term follow-up.

#### Primary outcome analysis

Primary outcome will be first analyzed on an intention-to-treat (ITT) basis, including all patients as originally allocated after randomisation. For missing information due to patient drop-out, we will rely on the linear mixed model and consider the baseline data as part of the outcome matrix. We will also perform a per-protocol (PP) sensitivity analysis including only those patients who completed the treatment originally allocated.

Analyses should be considered as hypotheses generating. To explore the effects of the intervention type on the two primary outcome measures, the results will be compared using linear mixed models. More precisely, the moment of the measure (baseline and immediate follow-up), the intervention (nested within the centers), the centers and the interaction of these factors will be considered as fixed factors. A nested random intercepts and slopes for each participant within the centers will be implemented. Age groups, educational level, objective Z-score (Z-score from 0 to -0.50; -0.51 to -1, etc.) and gender will also be included in the model as stratification factors. Following the linear mixed model, linear contrast will be performed between the two levels of the intervention variable on the first follow-up measure (T1) to explicitly compare the potential benefit of the intervention. Bonferroni adjustment will be performed to correct for multiple testing, more precisely 2 tests (the number of primary measures), and p-value < 0.025 will be considered as statistically significant. 95% CI and standardized effect sizes (SES) from the null model will be calculated. The following convention will be used to interpret effect size: small 0.2–0.49, moderate 0.5–0.79, large ≥ 0.8. As a Proof-of-Concept (POC) study, estimation will be focused on ES but will include p-values as help in interpreting the data.

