### Trial design

COVCOG is a multicenter, randomized controlled proof-of-concept trial conducted with two parallel groups (ratio 1:1) comparing psychoeducation interventions that focus on cognitive (*n* = 65) versus affective (*n* = 65) difficulties. Randomization with minimization will be used.

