### Study setting

The trial is conducted by the University of Liege in Belgium. The data are collected in Belgium at four centers: the university of Liège (the Psychological Clinic of University of Liege, CPLU and the university hospital, CHU-Liège), the university hospital of the University of Brussel (ERASME hospital), the regional hospital of Liege (CHR-Liège), and the catholic hospital of Liege (CHC-Liège).

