### Sample size

The uniqueness of our research does not make it possible to determine the exact expected effect size. Thus, we decided to follow a proof-of-concept study logic with a pragmatic approach to setting our sample size. A feasibility analysis led us to the conclusion that we could reach a sample of 130 participants in 10 months. We next measured the sensitivity of our experimental design on this expected recruitment rate with Gpower [54] based on the following values: alpha corrected for 2 primary outcomes equal to 0.025, power equal to 0.80, experimental design corresponding to a mixed analysis of variance with repeated measures and an intergroup variable, with an intra-subject correlation of 0.5. Results from the sensitivity analysis show that our experimental design will be able to detect small effect sizes (interaction effect in a mixed anova) of f = 0.137.

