### Assignment of interventions: allocation

#### Sequence generation

Given our small sample size, and because individuals with more severe cognitive impairments might respond differently to the intervention than those with milder difficulties, we will use randomization by minimization. Although severity and interval since COVID episode are probably important prognostic factors in outcomes, we decided to achieve trial arm balance only on age, education level, gender, Centre, and severity of cognitive deficits and complaints. For cognitive deficits, scores will first be Z-scored based on normative data, and next a global Z-score calculated on all variables will be considered (sum of Z-scores divided by number of measures). A Z-score will also be calculated for both tools assessing cognitive complaints. For both these objective and subjective indices, balance will be done by Z-score range of 0.5 (e.g., Z-score from 0 to -0.50; -0.51 to -1, etc.). For age we will use 18–29; 30–39; 40–49; 50–59; 60–70. For education, we will use 4 levels: 1. primary or professional education; 2. secondary education; 3. bachelor; 4. master. In the calculation of the imbalance each arm and each prognostic factor will have the same weight. The imbalance score is calculated based on all previous allocations as well as the current participant's hypothetical allocation to each treatment. The distance measure used to calculate the imbalance score is the marginal balance. If there is no imbalance, the allocation will be completely random. If there is an imbalance, the treatment with the lowest imbalance score is chosen with a 75% probability.

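### The primary model nests intervention within centres although the two are crossed, so it has no common intervention-by-time effect and the T1 contrast depends on centre weights that are not stated

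*Protocol article*

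**What the plan says.** **Model (Primary outcome analysis).** The fixed part consists of the moment of measure (baseline and immediate follow-up), then "the intervention (nested within the centers), the centers and the interaction of these factors will be considered as fixed factors". The random part is described as follows: "A nested random intercepts and slopes for each participant within the centers will be implemented". Age group, education, objective Z-score and gender are added as stratification factors.

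**Test (same section).** After the model, a "linear contrast will be performed between the two levels of the intervention variable on the first follow-up measure (T1"). It is judged at p < 0.025 for each of the two primary measures. No centre weights are given.

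**Design.** Trial design describes "two parallel groups (ratio 1:1) comparing psychoeducation interventions that focus on cognitive" and affective difficulties, with 65 patients per arm. Under Sequence generation, "we decided to achieve trial arm balance only on age, education level, gender, Centre, and severity of cognitive deficits and complaints", and "If there is an imbalance, the treatment with the lowest imbalance score is chosen with a 75% probability". Study setting adds: "The data are collected in Belgium at four centers". Numbers per centre are not given.

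**Sensitivity (Sample size).** The section expects that "we could reach a sample of 130 participants in 10 months". It reports a detectable interaction of f = 0.137 at alpha 0.025, power 0.80 and correlation 0.5, for a mixed ANOVA with one between-group variable. Centre is not mentioned.

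**The concern.** A factor is nested in centre when its levels belong to particular centres, for example therapists who each work at one site. Here the same two interventions are compared across the trial, and balancing the arms on centre makes sense only if both arms occur in each centre. The stated structure therefore does not describe the design.

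Two things are at stake. The first is the primary estimate. Without a common effect in the model, the comparison of the two arms is some average of four centre effects, and different averages give different answers and different precision. The second is the link to the sensitivity statement, which describes a single pooled interaction.

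The problem also spreads. Secondary outcome analysis re-runs the same model for the later time point and the other outcomes, and the subgroup analyses add a term to it.

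**Working it through.** **1. The plan's own figure.** For a within-between interaction with k = 2 groups, m = 2 times, N = 130 and rho = 0.5:

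- Noncentrality: lambda = f² × N × m / (1 − rho) = f² × 130 × 2 / 0.5 = 520 f².
- Degrees of freedom: 1 and 128; alpha 0.025.
- Solving for power 0.80 gives f = 0.1365. At f = 0.137, lambda = 9.76 and power = 0.803.

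The stated f = 0.137 is therefore reproduced, and the calculation behind it has no centre term.

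**2. What the stated model contains.** At one time point, 4 centres × 2 arms make 8 cell means. An intercept, 3 centre terms and 4 intervention-within-centre terms already use all 8. On simulated data for four centres:

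- The nested model and the crossed model with intervention-by-centre gave the same residual sum of squares (26.450). They are the same fit in different parameters.
- Four centre terms, four nested arm terms and one overall intervention column make 9 columns of rank 8. A separate overall intervention effect is not identified beside the nested ones, and an intervention-by-centre term would be redundant in the same way.

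**3. Weights change the estimate.** In that simulation, with sizes 65/30/20/15 and deliberately different centre effects, the four estimates were 0.522, 0.312, −0.025 and −0.417.

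- Equal weights: (0.522 + 0.312 − 0.025 − 0.417) / 4 = 0.098.
- Size weights: (65 × 0.522 + 30 × 0.312 − 20 × 0.025 − 15 × 0.417) / 130 = 0.281.
- Additive model with one common effect: 0.281.

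This is an illustration and not a forecast for this trial.

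**4. Weights change the precision.** Assume a 1:1 split in each centre and a common variance σ². With K centres of size n_k:

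- Equal-weight average: variance = (1/K²) Σ 4σ²/n_k.
- Common effect: variance = 4σ²/N.
- Ratio = (N/K²) Σ 1/n_k = (130/16) Σ 1/n_k = 8.125 Σ 1/n_k.

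Power is taken at f = 0.137 with lambda = 9.76 / ratio and 1 and 122 degrees of freedom (130 − 8). The sizes are assumptions.

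| Assumed sizes | Σ 1/n_k | Ratio | Effective N (130 / ratio) | Power | f detectable at 80% |
|---|---|---|---|---|---|
| 33/33/32/32 | 0.1231 | 1.00 | 130 | 0.80 | 0.137 |
| 50/40/25/15 | 0.1517 | 1.23 | 105 | 0.71 | 0.152 |
| 65/30/20/15 | 0.1654 | 1.34 | 97 | 0.66 | 0.158 |
| 80/20/20/10 | 0.2125 | 1.73 | 75 | 0.54 | 0.180 |

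**The case against.** The strongest reply is that nesting is only a parameterisation. The nested model spans the same space as the crossed model with interaction, an overall contrast can be estimated from it, and the plan does name an overall contrast between the two intervention levels. A size-weighted version of that contrast is available. Contrast weights are often left to the analysis plan or the full protocol, neither of which is shown. N was set by feasibility, and leaving centre out of a sensitivity calculation is ordinary simplification. The analyses are called hypothesis generating.

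Much of this stands, and it rules out several stronger readings that a reader might infer:

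- **That the contrast is equal-weighted.** The article does not say so. Equal weighting is the usual default and does not follow from nesting.
- **That power is lost.** This needs both equal weights and unequal centres. With equal centres there is no loss.
- **That the smallest centre would drive the result.** With equal weights each of four centres counts 25%.
- **That the model is rank deficient.** The interaction may mean time by intervention-within-centre, which is not redundant. Only an added intervention-by-centre term would be, and aliasing would not change the fit.
- **That the nested term would be tested jointly over four centres.** Power would then be 0.58 at f = 0.137, but the plan names a two-level contrast.

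What the reply does not remove is that the article itself states the fixed structure, and states it wrongly for this design. This is more than an omitted detail. Under either reading of the interaction there is still no common intervention-by-time effect, and the main result depends on a choice not yet made.

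**Conclusion.** The point holds as a mis-specification with an undefined contrast. Intervention is crossed with centre, the stated model gives four centre-specific arm effects, and the T1 contrast rests on unstated weights. The model also differs from the one behind f = 0.137.

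The cost in precision is conditional. It runs from none with equal centres to a variance ratio of 1.73 in the most uneven example. The 65/30/20/15 example gives 1.34 and power of about 66% instead of 80%. These figures assume equal weights, an even arm split within each centre, a common variance and no drop-out.

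Severity is moderate. The trial is a proof-of-concept focused on effect sizes, which softens the consequence. But the effect size is the very quantity left open, and p < 0.025 is still applied to it.

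**What to change.** Amend the primary model wording before any comparison of arms:

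- State intervention and centre as crossed.
- Use one common intervention-by-time effect, with centre and centre-by-time as fixed covariates. Keep the planned age, education, objective Z-score and gender terms.
- State whether the baseline arm means are constrained to be equal. Baseline is part of the outcome matrix, so this determines what the T1 contrast estimates.
- Report intervention-by-centre at T1 once, as an exploratory check of heterogeneity.
- If centre-specific effects are kept in the primary model instead, state size-based weights for the T1 contrast.
- Carry the same wording into the secondary and subgroup models that reuse this one.

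The cost is a wording change with no new data. The small downside is that centre-specific effects move to an exploratory table. With the common-effect model, the main test again corresponds to the pooled interaction in the sensitivity statement.

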### Eligibility criteria

All volunteers will be screened by a psychologist. To be included in the study, participants must meet the following criteria: be able to understand the information and consent forms; aged 18 to 70 years; medically stable and at least 3 months after a positive COVID 19 infection confirmed either by PCR, self-test or medical advice; report sufficiently good physical condition to attend the appointments; report no major hearing or vision disorders; report cognitive complaints (that place the person in the top 20% of dissatisfied functioning on the BRIEF or MMQ questionnaires); poor but not necessarily deficient objective performance (supported by a score below the 20th percentile on one task of the cognitive battery). Participants will be excluded if they have any chronic or remote neurological disorder (i.e. stroke, head trauma, epilepsy, tumor); preexisting cognitive impairment (associated with another minor or major neurocognitive disorder; intellectual disability); acute brain injury or acute encephalopathy from another etiology than covid (e.g., sepsis, liver or renal failure, alcohol or drug withdrawal, drug toxicity); documented preexisting history of psychiatric illness (including substance abuse); open-heart cardiac surgery or cardiac arrest during the last 6 months; current hospitalization; current revalidation care with cognitive treatment. Participants with preexisting neurological, cognitive, or psychiatric disorders (i.e., preceding COVID) are also excluded. Individuals with disorders co-occurring with COVID are not excluded.

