### Participant timeline

After a telephone screening, the patients corresponding to the eligibility criteria are invited to participate in the study with a first appointment for the baseline. The full assessment protocol is then administered. Individuals completing the inclusion criteria are randomized within one week of baseline and intervention can start the following week. The intervention sessions are proposed with a week interval followed by a reactivation session 1 month after the 4th session. Immediate and long-term follow-up will be administered 2 and 8 months after the end of intervention. This timeline is summarized in Fig. 1.

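### The primary mixed model gives each participant a random intercept and a random slope over only two moments, so with one score per moment its variance components cannot be separated

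*Protocol article*

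**What the plan says.** The Primary outcome analysis section names two levels for the time factor: "the moment of the measure (baseline and immediate follow-up". To handle drop-out, it will "consider the baseline data as part of the outcome matrix", so baseline is a row of the response and not a covariate. The random part is: "A nested random intercepts and slopes for each participant within the centers will be implemented". The treatment comparison is read at one time only: "linear contrast will be performed between the two levels of the intervention variable on the first follow-up measure (T1". Each of the two primary measures is tested at 0.025. No alternative covariance structure is named.

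The section on plans for assessment and collection of outcomes adds a second administration: "MMQ and BRIEF (primary outcome) will be remotely administered again after a 2-week interval to take account of fluctuating difficulties". Nothing says whether the two administrations are averaged, analysed as separate rows or left out, nor at which visits the repeat takes place.

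The Eligibility criteria section admits people on the primary scales themselves, with complaints "that place the person in the top 20% of dissatisfied functioning on the BRIEF or MMQ questionnaires".

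**The concern.** A random intercept and a random slope, each with its own variance and a covariance between them, plus a residual error, need more than two observations per participant. The protocol states this structure outright for a model it limits to two moments, so this is not a detail left open for a later document.

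Two things are at stake. The first is practical: software may reject the model, stop without converging, or report variance components that mean nothing. The statistician must then choose another structure during the primary analysis, with no rule to follow. The second depends on that choice. Dropping the slope is a natural step, but it forces one common variance on baseline and T1. The primary contrast uses T1 alone, so a wrong common variance goes directly into its standard error, confidence interval and p-value.

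**Working it through.** **Inputs.** From the protocol: two moments, a random intercept and slope, and a T1 contrast (Primary outcome analysis); 65 per arm (Trial design); "alpha corrected for 2 primary outcomes equal to 0.025, power equal to 0.80", within-subject correlation 0.5 and detectable f = 0.137 (Sample size). Assumed: the ratio r = SD at T1 / SD at baseline, because the document gives no SD.

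**1. The plan's own figure.** For the interaction in a two-group mixed ANOVA with m measurements, the noncentrality is f²·N·m/(1 − ρ), with (m − 1) and (N − 2)(m − 1) degrees of freedom. With N = 130, m = 2, ρ = 0.5 and alpha 0.025, power 0.80 is reached at f = 0.1365, which agrees with the stated 0.137 (power at 0.137 is 0.803). With m = 3 the result would be 0.122, and with m = 4 it would be 0.112. The sample-size section therefore counts two measurements per participant.

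**2. Counting parameters.** Code time as 0 and 1. Let g00, g01 and g11 be the intercept variance, covariance and slope variance, and s² the residual variance. The model implies:

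- variance at baseline: V11 = g00 + s²
- covariance: V12 = g00 + g01
- variance at T1: V22 = g00 + 2·g01 + g11 + s²

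The derivative matrix for (g00, g01, g11, s²) has rows (1, 0, 0, 1), (1, 1, 0, 0) and (1, 2, 1, 1). Its rank is 3, for 4 parameters. Adding c to s², subtracting c from g00, adding c to g01 and subtracting 2c from g11 leaves all three elements unchanged.

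**3. What that does and does not affect.** In one simulated data set with two rows per participant, residual variances of 0.01, 0.1, 0.2, 0.3 and 0.4 all gave the same log-likelihood (-361.09) and the same standard error of the T1 contrast (0.2043). The split is arbitrary. The contrast is not, because its variance, 2·V22/65, depends only on the identified V22.

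**4. The two-week repeats.** Entered as separate rows, they change the count:

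| Rows per participant | Covariance elements | Rank (4 needed) |
|---|---|---|
| One at baseline, one at T1 | 3 | 3 |
| One at baseline, two at T1 | 6 | 4 |
| Two at baseline, two at T1 | 10 | 4 |

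Averaging or dropping the repeats returns to the first line. The three-moment secondary model, with a slope linear in time, has 6 elements and rank 4, so the fault concerns the primary model.

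**5. The random-intercept fallback.** This model uses the pooled variance (SD0² + SD1²)/2 at both times. For the T1 contrast:

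- model SE / true SE = √[(1 + r²)/(2r²)]
- type I error = 2·[1 − Φ(2.2414 × that ratio)]

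For example, r = 1.2 gives √(2.44/2.88) = 0.920, and 2.2414 × 0.920 = 2.063, so the type I error is 3.9%.

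| Assumed r | Model SE / true SE | Type I error (nominal 2.5%) | Simulated |
|---|---|---|---|
| 0.8 | 1.13 | 1.1% | 1.2% |
| 1.0 | 1.00 | 2.5% | 2.6% |
| 1.1 | 0.96 | 3.2% | not run |
| 1.2 | 0.92 | 3.9% | 4.1% |
| 1.3 | 0.89 | 4.6% | 4.8% |
| 1.5 | 0.85 | 5.7% | 5.9% |

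The simulations used 40,000 trials per case, 65 per arm, correlation 0.5 and complete data. An unstructured 2x2 covariance gave 2.6% to 2.7% in every case. For the arm difference in change from baseline, with complete data, the random-intercept and unstructured standard errors coincide, so the problem is specific to the T1-only contrast.

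**The case against.** A reader might infer that the primary analysis cannot be carried out, or that its treatment estimate is invalid. The document does not support that. Only the split of the variance is undetermined. A random intercept and slope over two moments can reproduce the same marginal covariance as an unstructured matrix, so where software does return a fit, the T1 contrast and its standard error are the intended ones. This part of the objection stands.

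The second objection is that the repeats may be meant as rows: a time factor with two levels does not exclude two rows per level, and the model would then be identifiable. That is possible. The figure f = 0.137 favours one value per moment but does not settle how repeats enter the model. What remains is that the analysis section gives the repeats no role, and the written model works on only one of the possible readings.

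Third, a reader might infer that the type I error is inflated. The protocol never proposes a random-intercept-only model, and it gives no SD at either time. Selection on high complaint scores makes a narrower baseline plausible. But entry is on either questionnaire, so the narrowing on each scale is unknown. At equal SDs the fallback is correct, and with a smaller T1 SD it is conservative.

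Fourth, it is tempting to say that a repeat two weeks after baseline would be contaminated by treatment, since participants are "randomized within one week of baseline and intervention can start the following week". That is hypothetical, because the protocol does not say that the repeat is done at baseline.

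Finally, the analyses are declared hypothesis-generating, with the emphasis on effect size. That lowers the severity but does not remove the point: 0.025 is still the significance threshold and 95% intervals are still reported.

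**Conclusion.** The point holds in a limited form. With one score or one average per moment, the stated random-effects structure has 4 covariance parameters for 3 covariance elements and is not identifiable. This follows from the model as written and needs no assumed figure. The consequences are a possible refused or non-converging fit, an arbitrary variance split, and an unplanned choice of covariance structure. The T1 estimate itself is not biased.

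The effect on the standard error is conditional on two things: that the analyst retreats to a random intercept only, and that the T1 SD exceeds the baseline SD. For assumed ratios from 1.1 to 1.3, the standard error would be about 4% to 11% too small and the type I error about 3.2% to 4.6%. These ratios are assumptions, and the direction reverses below 1. Severity is moderate.

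**What to change.** State in the Primary outcome analysis section how the two-week administrations are used, and at which visits they take place, so that it agrees with the section on assessment and collection of outcomes. Then choose one of two forms:

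- **One score or one average per moment:** replace the random intercept and slope in the primary model by an unstructured 2x2 within-participant covariance, with separate variances at baseline and T1.
- **Repeats as separate rows:** say so explicitly and keep the random slope.

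Whether to average the two T1 administrations is a separate design preference; averaging does not cure the identifiability problem. Settle the wording before any unblinded analysis. The cost is a change of text in the protocol or analysis plan, with no new data and no change to the sample size.

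### The primary T1 contrast leaves baseline means free by arm, so it makes almost no use of baseline BRIEF/MMQ and gives up about 25% of the information at the protocol's own correlation of 0.5

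*Protocol article*

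**What the plan says.** The Primary outcome analysis section of the Protocol article fixes most of the model. To deal with drop-out it will "consider the baseline data as part of the outcome matrix". Besides the time of measurement (baseline and first follow-up), "the intervention (nested within the centers), the centers and the interaction of these factors will be considered as fixed factors". The test of interest follows the model fit: a "linear contrast will be performed between the two levels of the intervention variable on the first follow-up measure (T1"). No constraint on the baseline means is stated.

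For the allocation factors, the same section says: "Age groups, educational level, objective Z-score (Z-score from 0 to -0.50; -0.51 to -1, etc.) and gender will also be included in the model". Centre is already a fixed effect. The Sequence generation section has a longer list: "we decided to achieve trial arm balance only on age, education level, gender, Centre, and severity of cognitive deficits and complaints". It adds that "A Z-score will also be calculated for both tools assessing cognitive complaints", and that balancing uses bands 0.5 wide.

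The Sample size section works out sensitivity for a different quantity, the interaction in a mixed analysis of variance, with "alpha corrected for 2 primary outcomes equal to 0.025, power equal to 0.80", a within-subject correlation of 0.5 and a resulting f of 0.137.

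**The concern.** Putting baseline in the outcome vector looks like adjustment for baseline, but it adjusts the T1 comparison only if the two arms are given the same baseline mean. Here the intervention term and its interaction with time are both fitted, so each arm has its own mean at each time. With complete data, the estimated arm difference at T1 is then essentially the observed difference in T1 means, and the baseline questionnaire does almost nothing for it.

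Complaint severity is the one minimisation factor that does not enter the model as a covariate. It could have been carried by the baseline response, but with free baseline means it is not.

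What is at stake is the width of the interval. The trial's size was set by feasibility, and the article says that interpretation will rest mainly on effect sizes. A baseline score is planned for every patient, so precision that could be had from existing data is left unused.

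**Working it through.** **Inputs from the Protocol article.** 65 per arm, N = 130 (Trial design). Alpha 0.025 per primary outcome (two-sided in effect, as it is an F test), power 0.80, correlation ρ = 0.5 and f = 0.137 (Sample size). No other correlation is given.

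**Assumptions.** Equal SD at baseline and T1; simple-randomisation variance formulas; values of ρ other than 0.5; drop-out of 10–20%.

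**1. The plan's own figure.** For the group-by-time interaction with m = 2 measurements, the noncentrality is λ = f²·N·m/(1 − ρ), with 1 and 128 degrees of freedom. Solving for 80% power gives f = 0.1365, which agrees with the stated 0.137. At f = 0.137, λ = 0.018769 × 260 / 0.5 = 9.76 and power is 80.3%. With two arms and two times, this f is a difference in change of 4f = 0.548 SD.

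**2. Variance of the arm difference, in SD² units, complete data.**
- T1 contrast, free baseline means: 4/N = 4/130 = 0.0308, SE 0.175.
- Interaction (change score): 8(1 − ρ)/N = 4/130 at ρ = 0.5, SE 0.175.
- Common baseline mean, or analysis of covariance: 4(1 − ρ²)/N = 3/130 = 0.0231, SE 0.152.

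The information lost is ρ² = 0.25. Matching the adjusted analysis with the T1 contrast would take 130/0.75 = 173 patients, 43 more than planned. The 95% interval is 2 × 1.96 × 0.175 = 0.69 SD wide, against 2 × 1.96 × 0.152 = 0.60 SD. The article's small and moderate effect-size bands are each about 0.3 wide.

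**3. Detectable difference (80% power) and power at 0.548 SD**, from the noncentral t with 128 degrees of freedom. The T1 contrast stays at 0.546 SD and 80.3% whatever ρ is.

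| ρ | Loss | Detectable, interaction | Detectable, adjusted | Power, adjusted |
|---|---|---|---|---|
| 0.3 (assumed) | 9% | 0.646 | 0.521 | 84.2% |
| 0.4 (assumed) | 16% | 0.598 | 0.501 | 87.2% |
| **0.5 (protocol)** | **25%** | **0.546** | **0.473** | **90.8%** |
| 0.6 (assumed) | 36% | 0.489 | 0.437 | 94.8% |
| 0.7 (assumed) | 49% | 0.423 | 0.390 | 98.2% |

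**4. Does this survive the fuller model?** A generalised least squares simulation with centre and time-constant covariates gave losses of 26% (ρ = 0.5) and 50% (ρ = 0.7) against the common-baseline model.

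**5. Drop-out.** If a fraction p is seen at T1, the variance factors are ρ² + (1 − ρ²)/p with free means and (1 − ρ²)/p with a common mean. At ρ = 0.5 and p = 0.9 these are 1.083 and 0.833, a loss of 23%. At p = 0.8 they are 1.188 and 0.938, a loss of 21%.

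**6. Factors side by side.** Minimised on: age, education, gender, centre, objective deficit, complaints. In the model: age, education, gender, centre, objective deficit.

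**The case against.** The case for leaving the analysis alone is that nothing in it is invalid, and that stands. Several stronger readings are tempting, but the document does not support them.

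- **Bias or a false-positive problem.** Under randomisation the T1 contrast is unbiased. Minimising on complaint bands limits chance imbalance, and balancing on a factor without adjusting for it tends to make the model's standard error too large, which is conservative.
- **A broken sensitivity statement.** The Sample size section does treat a different test, but at ρ = 0.5 the interaction and the T1 contrast have the same detectable difference (0.546 SD), so the stated sensitivity holds. The two would part only at another correlation.
- **A loss of up to half.** That needs ρ of about 0.71, which appears nowhere in the document. Eligibility requires complaints in the top 20% on BRIEF or MMQ, which narrows the baseline range. In an illustrative simulation (selection on either scale, assumed correlation 0.6 between them), an unselected ρ of 0.5 fell to about 0.40, a 16% loss, and 0.7 fell to about 0.59, a 35% loss.
- **Baseline wholly ignored.** This is exact only with complete data. Patients missing T1 still contribute baseline under missing at random, which is the stated reason for the approach.
- **A separate defect in the omitted factor.** Baseline complaints are already a response in the model. Their absence as a covariate matters only because the baseline means are free.

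It may also be said that a statistical analysis plan could supply the constraint. That is possible. But the article does specify the fixed effects and the contrast, and as specified they leave the baseline means free. The exploratory, proof-of-concept framing lowers the urgency, yet it places the weight on estimation, where precision counts.

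**Conclusion.** The point holds as one of efficiency and should be fixed; it does not invalidate the analysis. As written, the primary contrast is essentially the unadjusted T1 difference when data are complete, and complaint severity is balanced in allocation but not adjusted for. At the protocol's correlation of 0.5, about a quarter of the available information is given up. The loss is smaller if the correlation is lower and larger if it is higher, and falls slightly to 21–23% with an assumed 10–20% drop-out. These sizes rest on equal variances at the two times and on simple-randomisation formulas. To the extent that minimisation balances complaints, the estimate will vary less than its reported standard error suggests, but the reported interval and test will not show that gain.

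**What to change.** In Primary outcome analysis, state one of two equivalent routes:

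- a mixed model in which both arms share the baseline mean: drop the intervention main effect (including its within-centre form at baseline), keep time and intervention-by-time, use an unstructured covariance for the two measurements, and take the intervention effect at T1 as primary; or
- analysis of covariance of the T1 score on the baseline score of the same questionnaire.

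Either brings complaint severity back through the questionnaire's own baseline, so no separate complaint covariate is needed. Covariate-by-time interactions are not needed either: main-effect covariates already shift the T1 mean, and the extra terms would cost parameters in 130 patients.

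In Sample size, name this T1 contrast as the quantity whose sensitivity is reported: 0.473 SD with 130 complete cases at ρ = 0.5.

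The cost is a change of wording. No new data, patients or visits are required, and randomisation justifies the common baseline mean.
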